### Data collection and monitoring

2.8

Designated outcome assessors, blinded to assignment, will record all measurements on case report forms (paper) and subsequently enter data into a secure electronic database (computerized CRFs). The Academic Committee of Yibin Traditional Chinese Medicine Hospital will function as the independent Data Monitoring Committee (DMC), supervising trial conduct and participant safety. The DMC is independent of the sponsor and the funder. No formal interim efficacy analysis is planned given the sample size. However, the DMC will conduct ongoing safety monitoring. In the event of any safety concerns or unexpected serious adverse events, the DMC is empowered to recommend trial modification or early termination. Data quality audits will be conducted monthly by independent monitors. The statistician performing the outcome analysis will remain blinded to group allocation until the primary analysis is complete. To promote participant retention, reminder phone calls and follow-up messages will be provided. For participants who discontinue or deviate from the intervention protocol, outcome data will continue to be collected at all scheduled time points whenever possible.

### Statistical analysis

2.9

All analyses will be conducted using SPSS (version 20.0, SPSS Inc., Chicago, IL, USA) with a two-sided significance level of *α* = 0.05. All analyses will follow the intention-to-treat(ITT) principle. Baseline characteristics will be summarized descriptively. The primary outcome, change in Cobb angle from baseline to week 12, will be compared between groups using Analysis of Covariance (ANCOVA), adjusting for the baseline Cobb angle. Results will be presented as adjusted mean differences with 95% confidence intervals. For secondary outcomes measured at multiple timepoints (ATR, ΔT, SRS-22r), linear mixed-effects models (LMMs) will be used to analyze the longitudinal data. The models will include fixed effects for time, group, and their interaction term, with participant as a random effect. The interaction effect will be examined to test if the change over time differs between groups.

Given the multiple secondary outcomes, we will control for multiple comparisons using the False Discovery Rate (FDR) approach (Benjamini-Hochberg procedure) across the secondary endpoints. Secondary outcome *p*-values will be adjusted using FDR at the 5% level to mitigate Type I error inflation. We will treat these analyses as exploratory; any inferences from secondary outcomes will be made with caution.

Missing data will be handled under the missing-at-random assumption using full information maximum likelihood (FIML) in the mixed-effects models. A multiple imputation approach will be performed as a sensitivity analysis to verify the robustness of results.

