## Introduction

1

Adolescent idiopathic scoliosis (AIS) is a structural, lateral, three-dimensional spinal deformity with onset during growth spurts in adolescence (1). If left untreated, moderate curves can progress, leading to cosmetic concerns, back pain, and psychosocial impairment (2). Severe untreated curves may progress and result in cardiorespiratory compromise (3). Conservative management, especially for mild-to-moderate curves, aims to halt progression and improve function without surgery (4). Schroth therapy is a scoliosis-specific exercise program focusing on three-dimensional corrective postural training, breathing techniques, and sensorimotor re-education. Evidence from randomized controlled studies indicates that Schroth exercises can reduce Cobb angle and improve trunk symmetry and quality of life in AIS patients (5–7).

Complementary therapies, including manual modalities, have been explored to enhance conservative management. Recent integration of manual therapies with scoliosis-specific exercise has shown promise; for example, combinations of spinal manipulation with Schroth have been evaluated with preliminary favorable findings (8, 9). Similarly, in China, Traditional Chinese Medicine (TCM) manipulation therapies such as Tuina are commonly used as conservative interventions for scoliosis (10). This approach employs soft-tissue relaxation techniques and spinal joint adjustments to rebalance paraspinal musculature and improve spinal alignment (11). This may alleviate pain and contribute to better overall patient outcomes.

However, current evidence remains limited. Most existing studies investigating manual therapies for scoliosis are preliminary, with small sample sizes, heterogeneous interventions, and methodological shortcomings that restrict the generalizability of their findings (12). Therefore, this study is designed to test the hypothesis that combining TCM manipulation with the Schroth method will yield superior improvements in spinal curvature, postural control, and pain reduction compared with the Schroth therapy alone. This trial aims to provide rigorous clinical evidence for the integration of TCM manipulation into evidence-based conservative management of AIS.

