#### Inclusion criteria

2.2.1

Eligible participants who meet the following criteria will be included:(i) Diagnosed with AIS; (ii) Cobb angle between 10° and 45°; (iii) Age 10–18 years, any gender; (iv) Able to provide informed consent (parental/guardian consent where applicable) and comply with follow-up; (v) Able to undergo interventions, spinal radiography, and infrared thermography; (vi) Not currently in a scoliosis bracing program or requiring immediate bracing at the time of enrollment. (vii) No other concurrent scoliosis treatment during study period.

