#### Adverse events

2.3.3

Adverse events are defined as any untoward medical occurrence in a participant, and will be categorized by severity (mild/moderate/severe) and relatedness to the intervention. Serious adverse events (SAEs) are defined as events that are life-threatening, require/prolong hospitalization, or result in significant disability or harm.

Adverse events will be systematically assessed at each study visit. Participants will be specifically asked about musculoskeletal discomfort, skin reactions, and neurological symptoms. All adverse events will be recorded, graded, and reported to the ethics committee as per institutional policy. Serious adverse events will trigger immediate review. The trial may be terminated based on the findings of this review. Participants who experience trial-related adverse events will receive free emergency medical care by the investigators.

Additionally, disease progression will be closely monitored as a key safety parameter. All participants will be regularly assessed for clinical signs of worsening, such as increased Angle of Trunk Rotation (ATR) or observable postural changes. If significant clinical deterioration is suspected, a follow-up radiograph will be obtained to confirm progression. Upon confirmation of radiological or significant clinical worsening, the study protocol includes provisions to withdraw the patient from the trial and ensure they receive appropriate standard care.

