### Randomization and allocation concealment

2.4

The allocation sequence will be generated using a permuted block design (random block sizes of 4 and 6) and will be stratified by baseline curve severity (Cobb angle ≤25° vs. >25°) to ensure balance in scoliosis severity between groups. This stratified block randomization will be implemented by an independent statistician. To ensure concealment, the sequence will be embedded into a sequentially numbered, opaque, sealed envelope (SNOSE) system, which will be prepared and safeguarded by an independent research coordinator. After baseline assessment, the coordinator will open the next consecutive envelope to assign the participant to a group. This process will ensure that recruiters and therapists remain unaware of the allocation sequence until after the participant has been assigned to a group.

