#### Primary outcome

2.6.1

Change in the Cobb angle (degrees) of the major structural curve (defined as the curve with the largest Cobb angle), will be measured on full-length standing anteroposterior spine radiographs at weeks 0 and 12 only. A fixed tube-to-detector distance of 200 cm, with pelvic leveling blocks used if necessary to compensate for leg length discrepancy. All measurements will be performed by two independent readers blinded to participant allocation and time point. A consensus process with a third adjudicator is predefined for discrepancies greater than 3°. The intra- and inter-rater reliability of the measurements will be formally assessed using intraclass correlation coefficients (ICCs).

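### The primary ANCOVA adjusts for baseline Cobb angle alone; pre-specifying age as a second covariate would be a nearly free, modest gain in precision in a trial of 10- to 18-year-olds

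*Protocol article*

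**What the plan says.** All references are to the protocol article.

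- **Eligibility (2.2.1):** "Age 10–18 years, any gender".
- **Disease description (Introduction):** AIS is a "three-dimensional spinal deformity with onset during growth spurts in adolescence". The same paragraph says that moderate curves can progress if untreated.
- **Progression within the trial (2.3.3):** "disease progression will be closely monitored as a key safety parameter".
- **Allocation (2.4):** the sequence "will be stratified by baseline curve severity (Cobb angle ≤25° vs. >25" degrees. No other factor is named.
- **Primary outcome (2.6.1):** Cobb angle on "full-length standing anteroposterior spine radiographs at weeks 0 and 12 only".
- **Primary analysis (2.9):** change in Cobb angle "will be compared between groups using Analysis of Covariance (ANCOVA), adjusting for the baseline Cobb angle".
- **Other baseline data (2.9):** "Baseline characteristics will be summarized descriptively".

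Age or a measure of maturity does not appear in the stratification, in the primary model or in the one stated sensitivity analysis, which is multiple imputation.

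**The concern.** Baseline Cobb angle records how large the curve is. It does not record how much growth a participant has left. With an eight-year age span in a condition whose onset the article ties to growth, age may carry information about Cobb change that baseline Cobb lacks.

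If it does, there are two consequences, and both are aspects of the same loss. Variation in outcome that age could explain stays in the residual and widens the confidence interval. And if the arms happen to differ in age, the adjusted mean difference moves with that imbalance and the model cannot take it out. In addition, if age is not named in advance and the arms turn out uneven, any later adjustment for it becomes a post hoc choice.

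The planned power has little slack, so even a small gain in precision is of some use.

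**Working it through.** **Inputs from the article (section 2.7).** Standardised effect 0.81; difference 4° to 5°; two-sided α 0.05; power 80%; 25 per arm evaluable; 30 per arm randomised; attrition about 20%. The implied SD is 4/0.81 = 4.94° to 5/0.81 = 6.17°.

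**Input not in the article (assumption).** The correlation r between age and 12-week Cobb change, given baseline Cobb. A range of 0 to 0.5 is shown. The conclusion uses 0.1 to 0.3.

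**1. The plan's own figure.** A two-sample t-test (noncentral t) with effect 0.81 and 25 per arm has power 80.1%, so the stated 25 per arm reproduces. If 20% of 60 are lost, 48 remain (24 per arm), and power is 78.4%.

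**2. Power with age added.** The residual SD is multiplied by √(1 − r²), so the effect becomes 0.81/√(1 − r²), and one degree of freedom is deducted for age. The 0.81 is taken as the standardised effect before age is added.

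| r | Residual variance removed (r²) | Power, 24 per arm | Power, 25 per arm |
|---|---|---|---|
| Without age | – | 78.4% | 80.1% |
| 0 | 0% | 78.4% | 80.1% |
| 0.1 | 1% | 78.8% | 80.5% |
| 0.2 | 4% | 80.0% | 81.7% |
| 0.3 | 9% | 82.1% | 83.7% |
| 0.4 | 16% | 85.0% | 86.4% |
| 0.5 | 25% | 88.7% | 89.9% |

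For r = 0.1 to 0.3 the gain runs from 0.4 points (78.8 − 78.4; 80.5 − 80.1) to 3.7 points (82.1 − 78.4) at 24 per arm, or 3.6 points (83.7 − 80.1) at 25 per arm. At r = 0 the lost degree of freedom does not show at one decimal place.

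**3. Size of chance imbalance.** With no balancing on age, the standardised age difference between arms has SD √(2/30) = 0.26, so its 95% range is ±0.51. It exceeds 0.25 SD in about 33% of randomisations and 0.5 SD in about 5%. The resulting movement in the Cobb difference has 95% range ±1.96 × r × SD × √(2/30):

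- r = 0.1: ±0.25° to ±0.31°
- r = 0.3: ±0.75° to ±0.94°
- r = 0.5: ±1.25° to ±1.56°

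These compare with a planned difference of 4° to 5° and the article's minimal clinically important difference of 3.5°.

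**4. What the assumed r means in degrees.** If ages were uniform over 10 to 18 (assumption), the age SD is 8/√12 = 2.31 years. The slope is r × SD / 2.31. For r = 0.1 it is 0.21° to 0.27° per year, or about 1.7° to 2.1° across eight years. For r = 0.3 it is 0.64° to 0.80° per year, or about 5.1° to 6.4° across eight years. The upper end of the range therefore already supposes an age gradient at least as large as the planned treatment effect, within 12 weeks. Larger values of r are hard to argue from this article.

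**5. Validity.** In 20,000 simulated trials with 30 per arm and no treatment effect, the Cobb-only ANCOVA rejected in 4.7% (r = 0.3) and 4.9% (r = 0.5). With age added it rejected in 4.8% in both cases. Omitting age leaves the test at its nominal level.

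**The case against.** **The stated model is valid.** ANCOVA on the baseline value of the outcome, with randomisation stratified on that same measure, is sound, and a further covariate is a matter of efficiency. This stands, and it limits the point to an optional improvement.

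**A reader might infer that the article describes a growth-driven disease, so that 12-week change must differ by age.** The text does not go that far. The Introduction ties onset to growth spurts and links progression to untreated moderate curves. The Discussion mentions skeletal maturity only as the horizon for future studies. No section says that 12-week Cobb change varies with age, and no participant is untreated, since both arms receive Schroth therapy. The relation is possible but not documented.

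**A reader might also infer bias or a raised false-positive rate.** Neither follows. Randomisation protects the comparison, the simulation confirms the error rate, and the confidence interval already allows for chance imbalance. The shift in the estimate and the wider interval should not be counted as two separate harms.

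**The magnitude rests on assumptions.** This is correct. For example, the chance of a mean age gap of at least one year at 30 per arm is about 9% if the age SD is 2.31 years (SE 0.596), but about 1% if it is 1.5 years (SE 0.387). A single linear age term may also miss part of a non-linear growth effect, in which case r for that term is at the low end.

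**The SAP may already deal with it.** The article says a SAP is available on the registry, and it is not shown here. But the article does not leave the primary model open: it names the model and a single covariate, and the comment is on that stated choice. If the SAP already includes age, the two documents only need to be aligned.

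**Conclusion.** The point holds as a modest, nearly free gain in precision. The article fixes a primary model with baseline Cobb as its only covariate, in a population aged 10 to 18, and age is known for every participant because it decides eligibility. For an assumed partial correlation of 0.1 to 0.3, adjustment removes 1% to 9% of residual variance and adds about 0.4 to 3.7 points of power at 24 to 25 per arm. At zero correlation it gains nothing and costs almost nothing.

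The conclusion rests on that assumed correlation, on a linear age effect, and on the article's effect size of 0.81. The planned analysis remains valid without the change, and the design is not undermined.

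**What to change.** Before unblinding, name age at randomisation (continuous, in years) as a second covariate in the primary model, so that section 2.9 reads in substance: ANCOVA adjusting for baseline Cobb angle and age. Keep the Cobb-only ANCOVA as a sensitivity analysis and report both.

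The cost is one degree of freedom and one line of text. No new data, strata or change in sample size are needed, and it can still be done although recruitment has begun. Because the article says important modifications go to the ethics committee and the registry, the change should be recorded there with its date, so that it is clearly made before any unblinded look at outcomes. Adding age as a stratum is less attractive: with 60 participants and two Cobb strata already, a covariate is the simpler route.

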**Methods:**

This is a single-center, randomized controlled, two-arm parallel-group superiority trial. Sixty adolescents (aged 10–18) with idiopathic scoliosis and Cobb angle 10°–45° will be randomized 1:1 to: (1) Schroth therapy alone (control) or (2) TCM manipulation combined with Schroth exercise (intervention). Primary outcome is change in Cobb angle measured by full-length standing anteroposterior spinal radiograph before and after the intervention. Secondary outcomes include Angle of Trunk Rotation (ATR), paraspinal thermal asymmetry assessed by infrared thermography, and health-related quality of life measured by the Scoliosis Research Society-22r (SRS-22r) questionnaire. Participants will be randomly allocated (1:1) using a computer-generated, stratified block randomization sequence with allocation concealed by sealed opaque envelopes. The analysis will follow the intention-to-treat (ITT) principle, and an ANCOVA adjusting for baseline measurements will be used for between-group comparisons. A total sample size of 60 participants (30 per group) was determined *a priori* to provide 80% power (*α* = 0.05, *β* = 0.20) to detect a clinically meaningful difference in Cobb angle, allowing for a 20% attrition rate.

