### Sample size

2.7

The sample size was determined *a priori* using G*Power software (version 3.1.9.7). Based on the primary outcome of change in Cobb angle, an effect size of 0.81 was derived from a previous randomized controlled trial (15). This effect size corresponds to a between-group difference of approximately 4°–5° in Cobb angle improvement. We consider this difference clinically meaningful as it exceeds both the typical measurement error (∼3°) and the established minimal clinically important difference (MCID) of 3.5° for non-operative interventions in AIS (16). The calculation was performed for a two-tailed independent-samples *t*-test, with an alpha (α) error level set at 0.05 and a beta (β) error level set at 0.20 (statistical power of 80%). The result indicated that a total of 50 participants (25 per group) would be required to detect the anticipated effect. To account for a potential attrition rate of approximately 20% throughout the trial period, the target sample size was increased to 60 participants (30 per group) to ensure adequate statistical power for the final analysis.

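### The secondary mixed models keep baseline as a free outcome and test only the group-by-time interaction, which costs some precision and does not isolate the week-12 difference

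*Protocol article*

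**What the plan says.** Section 2.9 gives the terms of the secondary models: "The models will include fixed effects for time, group, and their interaction term, with participant as a random effect". It then names the test: "The interaction effect will be examined to test if the change over time differs between groups". It names no baseline covariate, no coding of time, no residual covariance structure and no contrast at a particular visit. Secondary p-values go through the Benjamini-Hochberg procedure at 5%, and these analyses are labelled exploratory.

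The abstract reads differently. It says that "an ANCOVA adjusting for baseline measurements will be used for between-group comparisons" and does not limit this to the primary outcome. In section 2.9, ANCOVA is used for Cobb angle alone.

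Sections 2.6 and 2.6.2 place the secondary assessments at weeks 0, 2 and 12. Week 2 was added to capture the immediate effect of the inpatient phase. Table 1, as reproduced, marks ATR at weeks 0 and 2 only. Sections 2.3.1 and 2.3.2 confine TCM manipulation to the first two weeks; after that both arms follow the same home Schroth programme.

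**The concern.** Three features of the stated model fit this design poorly.

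- **Baseline.** With week 0 as a response and a free group effect there, the group-by-time term at week 12 equals the between-arm difference in raw change. Randomisation makes the true baseline difference zero. Estimating that difference freely discards information already collected, which matters with about 25 evaluable participants per arm.
- **The test.** With three visits and categorical time, the interaction has 2 degrees of freedom and responds to any difference in profile. Manipulation stops at week 2, so an early difference that fades is a foreseeable result. A significant interaction would not tell the reader whether any benefit remains at week 12.
- **The covariance.** A participant random intercept with independent residuals implies the same correlation for visits 2, 10 and 12 weeks apart. If correlation falls with the interval, a week-12 interval taken from this model would be too narrow.

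**Working it through.** **Inputs.** From the article: visits at weeks 0, 2 and 12; two-sided α = 0.05; 25 evaluable per arm (section 2.7). The plan's own figure reproduces: for d = 0.81, a two-sample t-test has 80.1% power at 25 per arm and 78.4% at 24. That calculation concerns Cobb angle only and is used here just to set n = 25. The article gives no between-visit correlations or effect sizes for the secondary outcomes, so those below are assumptions, with outcomes scaled to SD 1.

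**1. Precision lost by not adjusting for baseline.** Let ρ be the week 0 to week 12 correlation.
- Per-participant variance of the change score: 2(1 − ρ).
- Per-participant variance after baseline adjustment: 1 − ρ².
- Ratio: 2(1 − ρ)/(1 − ρ²) = 2/(1 + ρ).

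| ρ | 2(1 − ρ) | 1 − ρ² | Variance ratio | SE ratio |
|---|---|---|---|---|
| 0.5 | 1.00 | 0.75 | 1.33 | 1.155 |
| 0.6 | 0.80 | 0.64 | 1.25 | 1.118 |
| 0.7 | 0.60 | 0.51 | 1.18 | 1.085 |
| 0.8 | 0.40 | 0.36 | 1.11 | 1.054 |
| 0.9 | 0.20 | 0.19 | 1.05 | 1.026 |

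In simulation with ρ = 0.7 and an assumed week-12 effect of 0.6 SD, power is 77% for the change contrast and 82-83% for ANCOVA.

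**2. What a significant interaction would show.** Assume a 0.6 SD effect at week 2 and none at week 12, with categorical time and a random intercept. Under equal correlations of 0.7, the noncentrality is (n/2) × Σ(δ − mean δ)²/(1 − ρ). The effects over the three visits are 0, 0.6 and 0, so Σ(δ − mean δ)² = 0.6² × 2/3 = 0.24. The noncentrality is 12.5 × 0.24/0.3 = 10. Simulation gives a significant interaction in about 80% of trials. With correlations (weeks 0-2, 0-12, 2-12) of 0.85/0.70/0.70 it is about 90%, and with 0.90/0.70/0.75 about 97%.

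**3. Standard error of a week-12 contrast under a random intercept alone.** With complete data, the model's residual variance estimates 1 − (mean of the three correlations). The correct quantity for the week 0 to 12 contrast is 1 − ρ(0-12). The ratio of model SE to true SE is the square root of their quotient.
- 0.90/0.70/0.75: mean 0.783; √(0.217/0.30) = 0.85, so the SE is 15% too small.
- 0.85/0.70/0.70: mean 0.75; √(0.25/0.30) = 0.91, so the SE is 9% too small.
- Equal correlations: ratio 1, so no error.

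The corresponding type I error, 2[1 − Φ(1.96 × ratio)], is 9.6% and 7.4%. Simulation gives 9.5-9.7% and 7.1-7.3%, and 4.9-5.0% under equal correlation.

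**4. The interaction test itself.** Across the same kinds of pattern, the 2-df test has type I error between about 4.9% and 6.3%. It is barely affected.

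**5. Stratum term.** In mixed-model fits with complete data, adding the stratum as a main effect left the interaction estimate and its SE unchanged (mean SE 0.2208 with and without). With 20% loss at week 12 the mean SE moved from 0.2295 to 0.2293, under 0.1%.

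**The case against.** The planned model is common and valid. Because week 0 is a response, the interaction removes baseline differences, so a reader who infers that the plan ignores baseline would be wrong: only precision is at stake. This stands, and the point is confined to it.

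A reader might also infer that leaving the stratification factor out costs precision. It does not. A term that is constant over time cancels from within-person change (step 5), and the primary ANCOVA already adjusts for continuous baseline Cobb angle, the variable that defines the strata.

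Nor can the 7-10% error rate be charged to the plan's named test. It belongs to a week-12 contrast that section 2.9 does not specify.

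It is fair, too, that the text neither says that the random intercept is the only covariance term nor states the coding of time, and that a full analysis plan may settle both. The covariance and 2-df points are therefore conditional. Linear time would avoid 2 degrees of freedom, but it would force one straight line through an intensive phase and a home phase.

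Week 2 is measured on purpose, so detecting an early difference is a legitimate aim. The interaction test is also not uniformly weaker. With equal correlations of 0.7 and 0.6 SD at week 12, its power is about 80% against 78% for the week-12 contrast when the week-2 effect is full or absent, and 68% against 78% when it is half. What remains is interpretation: one p-value cannot separate an early effect from a lasting one.

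**Conclusion.** The point holds as a modest improvement to exploratory secondary analyses; the primary ANCOVA is unaffected. The firm part is that the stated model forgoes baseline adjustment. Its variance is 11-33% larger for ρ from 0.8 to 0.5 and only 5% larger at ρ = 0.9, and the abstract describes a different analysis. Two parts are conditional. If time is categorical, the interaction can be significant from a transient week-2 difference, in 80-97% of trials under the assumed 0.6 SD effect and correlations. If the random intercept is the sole covariance term and correlation decays, a week-12 contrast would have an SE 9-15% too small and type I error of about 7-10%. Under equal correlation that problem disappears. The documents do not support a claim of bias, of a material error rate in the named interaction test, or of precision lost by omitting the stratum.

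**What to change.** In section 2.9, for ATR, ΔT and SRS-22r:

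- Model weeks 2 and 12 with the baseline value as a covariate, or keep all three visits and constrain the baseline means to be equal across arms.
- State that visit is categorical and that the within-participant covariance is unstructured.
- Report the adjusted between-group difference at week 12 with its 95% confidence interval as the result entering the Benjamini-Hochberg procedure, with the week-2 difference alongside.

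Reconcile the abstract's ANCOVA statement with section 2.9. Reconcile Table 1 with section 2.6.2 on whether ATR is measured at week 12, since the week-12 ATR contrast depends on it.

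The cost is analysis wording only. No extra data are needed, and the planned software can fit these models. The downside is a few more covariance parameters: over three visits, six (three variances and three correlations) instead of the two of a random-intercept model.

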### Outcomes

2.6

To minimize radiographic exposure, outcome measures will be assessed at different timepoints based on their invasiveness and clinical practicality. All outcomes will be assessed at baseline (week 0) and study completion (week 12). Additionally, to capture the immediate effects of the intensive inpatient intervention, all secondary outcomes will also be assessed immediately following the 2-week intensive intervention period (week 2).

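### Read literally, FIML means maximum likelihood fitting of the secondary-outcome mixed models, which makes their standard errors about 2% too small; REML removes this at almost no cost

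*Protocol article*

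**What the plan says.** Section 2.9 plans linear mixed models for the three secondary outcomes. Their structure is given as: "The models will include fixed effects for time, group, and their interaction term, with participant as a random effect". The tested effect is the interaction: "The interaction effect will be examined to test if the change over time differs between groups". Section 2.6 gives three assessments, at weeks 0, 2 and 12.

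Estimation is mentioned only in the paragraph on incomplete data, which assumes missing at random and handles the gaps "using full information maximum likelihood (FIML) in the mixed-effects models". Multiple imputation follows as a sensitivity analysis. The article mentions neither REML nor a degrees-of-freedom method.

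Secondary p-values are to be "adjusted using FDR at the 5% level to mitigate Type I error inflation". The authors add: "We will treat these analyses as exploratory; any inferences from secondary outcomes will be made with caution". The primary outcome, Cobb angle change at week 12, is analysed separately by ANCOVA.

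**The concern.** ML estimates a variance by dividing residual variation by a count that ignores the fixed effects already estimated from the same data. The estimate is therefore too low on average in small samples, and so are the standard errors built on it. REML makes the deduction. REML is also likelihood-based, uses every available observation and is valid under the same missing-at-random assumption, so ML buys nothing for the missing data.

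At stake are the p-values and confidence intervals of the secondary outcomes. The p-values are also the input to the Benjamini-Hochberg procedure, which the plan adopts to restrain false positives. An estimator that puts a little inflation back works against that aim.

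**Working it through.** **Plan's own figures.** The article states no standard error or test size for the mixed models, so there is none to reproduce. Its sample size does reproduce: effect size 0.81, two-sided 5%, t-test, 25 per group gives 80.1% power (section 2.7).

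**Inputs.**
- N = 60 randomised 1:1 (section 2.7).
- N = 60 × 0.8 = 48 after the 20% attrition allowed for in section 2.7. This is close to a worst case, because the mixed models also use participants with partial data.
- T = 3 visits (section 2.6), with time taken as categorical (assumption), so the interaction has 2 degrees of freedom.
- Two-sided alpha 0.05 (section 2.9).
- Within-participant correlation: not given. Assumed 0.5 and 0.8, in the simulation only.

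**Standard error.** For complete data and a random intercept, let SSW be the within-participant residual sum of squares.
- ML residual variance = SSW / (2N)
- REML residual variance = SSW / (2(N − 2))
- SE ratio, ML to REML = √((N − 2)/N)

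N = 48: √(46/48) = 0.979, or 2.1% too small. N = 60: √(58/60) = 0.983, or 1.7% too small.

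**Size of the interaction test.** Using ML multiplies the valid F statistic by N/(N − 2), so the true size is P[F(2, d) > c(N − 2)/N], with d = 2(N − 2) and c the 5% critical value. With 2 numerator degrees of freedom, P[F > x] = (1 + 2x/d)^(−d/2).
- N = 48: d = 92, c = 3.095, 3.095 × 46/48 = 2.966, size = (1 + 5.932/92)^(−46) = 5.64%.
- N = 60: d = 116, c = 3.074, 3.074 × 58/60 = 2.972, size = (1 + 5.944/116)^(−58) = 5.51%.

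If the denominator degrees of freedom are also taken as 2N, the sizes are 5.66% and 5.53%. REML gives 5.0% in each case. For a single contrast such as week 12, ML gives 5.5% (N = 48) and 5.4% (N = 60).

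**Simulation with missing data** (4,000 trials per setting, Monte Carlo error about 0.35 points; correlation 0.5, then 0.8):

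| Setting | ML rejects | REML rejects |
|---|---|---|
| N = 60, complete | 5.0%, 5.7% | 4.6%, 5.3% |
| N = 60, about 20% MAR dropout at week 12 | 5.7%, 5.8% | 5.2%, 5.2% |
| N = 48, complete | 5.6%, 5.6% | 4.9%, 5.1% |

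The mean bias of the week-12 contrast was near zero and the same for both estimators in every setting. REML therefore gives up nothing under missing at random here.

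**False discovery rate.** Benjamini-Hochberg was applied to the ML p-values, with independent endpoints and an F reference (400,000 runs):

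| Endpoints | Real effects | N = 48 | N = 60 |
|---|---|---|---|
| 3 | none | 5.9% | 5.7% |
| 3 | one, strong | 3.8% | 3.7% |
| 7 | none | 6.1% | 5.9% |
| 7 | one | 5.1% | 5.0% |
| 7 | two | 4.2% | 4.0% |

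Seven is an assumption: three ATR levels, three muscles for ΔT and one SRS-22r score. The procedure's nominal rate is 5% times the share of true nulls, so each real effect leaves room that absorbs the inflation.

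**The case against.** The strongest reply is that the quoted sentence concerns missing data, not the fitting criterion. The FIML label is often used loosely for any likelihood analysis of all available observations under missing at random, so REML is not clearly excluded. The article also says that a full protocol and analysis plan exist; these are not shown and may settle the matter. The effect is tiny, the outcomes are exploratory, and multiple imputation is planned as a check.

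Most of this stands and limits the weight of the point. The absence of a degrees-of-freedom method is not counted as a fault, since a condensed article may leave it out. But the estimator is not an omission: the article names one, its literal meaning is ML, and the two readings give different standard errors. Saying which is meant is worth a sentence.

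Three stronger readings are tempting, and the documents do not support them.
- **A size of 5.9% (N = 60) to 6.2% (N = 48).** This needs a Wald chi-square reference, which the article never states. With that reference REML itself gives 5.4% to 5.5%, so nearly half of the excess comes from the reference distribution, not from ML.
- **A size of 6.0% to 7.1% at N = 48.** This assumes an unstructured within-participant covariance. Section 2.9 specifies only a participant random effect. The upper figure also adds the chi-square reference.
- **Failure to hold the 5% false discovery rate.** As a general statement this is wrong. With three endpoints the rate was exceeded when every null was true, by less than one point, and fell below 5% with one strong real effect.

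**Conclusion.** The point holds in a limited form. If FIML is taken at its word, the secondary-outcome standard errors are about 1.7% to 2.1% too small, the nominal 5% group-by-time F test runs at about 5.5% to 5.7%, and the 5% false discovery rate may be slightly exceeded, mainly when all or most secondary nulls are true. This rests on the stated random-intercept model, categorical time with three visits, an F reference, and between 48 and 60 participants. The closed form assumes complete data; the simulation with dropout agrees with it within Monte Carlo error.

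A reader might infer that the secondary results would be unreliable. They would not: the effect would rarely change a conclusion, point estimates showed no difference in mean bias, and the primary ANCOVA is untouched. It is a cheap improvement.

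**What to change.** Replace the FIML clause in section 2.9, or settle it in the analysis plan before analysis, with wording such as:

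> The mixed models will be fitted by restricted maximum likelihood (REML) to all available observations, valid under missing at random, with a small-sample degrees-of-freedom method available in the software used (for example Satterthwaite) for tests and 95% confidence intervals.

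Keep ML only where models with different fixed effects are compared by likelihood ratio. The cost is one sentence and secondary intervals wider by 1/0.983 = 1.017 (N = 60) to 1/0.979 = 1.021 (N = 48), that is about 2%. No change to the design, the data collection or the primary analysis is needed.
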